#### Outcome measures

The primary outcome measure was the incidence of AEs (sum of the incidence of pressure ulcers, urinary tract infections and falls).

A *pressure ulcer *is an area of localised damage to the skin and underlying tissue caused by a combination of pressure and shear[21]. Pressure ulcers are classified in four grades according to the guidelines [19,21,40]. Pressure ulcers were considered present if a patient developed a PU grade 2 or worse. If a patient had a PU grade two or worse at the first visit, that PU lesion was excluded from the registration of PUs until the PU healed. Patients with an already present PU grade two or worse were only registered if they developed additional PU lesions.

A *urinary tract infection *is bacteriuria with clinical symptoms as: frequent urinating, pain while urinating, abdominal pain, fever and delirium, urinary incontinence [18,24]. During this study we defined a urinary tract infection as present if it was diagnosed by a medical doctor. Patients were excluded from the registration of urinary tract infection for a period of three weeks if they had a urinary tract infection until the infection was cured.

A *fall *is an unexpected event in which the participant comes to rest on the ground, floor, or lower level [20,41]. In this study the falls were measured by examining the patient files, assuming that if a patient fell it was reported in his or her file.

The secondary outcome measures were 1) the percentage of patients that received preventive care and 2) the knowledge of nurses regarding the three topics.

*Prevention *is important in patients at risk for one of the AEs. Preventive measurements were considered present when the care was performed according to the guideline.

The risk of *pressure ulcers *was measured with the PrePURSE [27] and the Braden scale [42] in hospitals and nursing homes, respectively. Next preventive care was measured: position while lying or sitting; if patients' heels were lifted; use of pressure-reducing material or alternating pressure material in bed or chair; presence of a repositioning scheme.

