#### Statistics

Power calculation was based on the primary outcome, with a two-sided alpha of 0.05 and 80% power for the analysis of both the hospital and the nursing homes data.

As randomisation was on ward level, a ward was considered to be a cluster. To account for these clusters an intra class correlation coefficient of 0.01 was used in the calculation.

In hospitals, the incidence of pressure ulcers (10%) will be the highest contributor to our combined AE measure. The incidence of urinary tract infection and falls in the same patients is unknown. Therefore we assumed that the count of these three AEs will be 12% (an additional 1% for falls and 1% for urinary tract infections). We aimed to achieve a reduction of 50% as studies on the prevention of pressure ulcers have shown this is attainable [45,46]. To detect a decrease in AEs (from 12% – 6%) 1250 patients had to be included in each hospital group.

In the nursing homes, the incidence of falls will be the highest (60%). We assume that the additional contribution of pressure ulcers and urinary tract infection to AEs will be negligible. We aimed to achieve a reduction of 60% as a study on the prevention of falls showed this was attainable [47]. Therefore this study wanted to achieve a reduction of AEs from 60 – 36%. To detect this decrease in the nursing homes, 100 patients had to be included in each group.

The results will be analysed separately for hospitals and nursing homes, as patient characteristics, length of stay and nurse characteristics differ between hospitals and nursing homes.

The difference in incidence of AEs between the intervention and the control group during the follow up period will be analysed using a random effects Poisson regression analysis, including the following covariates: ward (random effect), institution and the baseline results of the ward.

The secondary outcomes will be evaluated in a similar way, using linear and logistic random effect models.

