The implementation of the digital registration and feedback system was even more complex. Currently, registration of patient care in a computer is not a standard procedure in the Netherlands. The nursing files are still mainly paper files. Moreover, not all nurses of the participating wards were used to working with a computer and on some wards the nurses did not even have access to a computer or the internet. We explored these barriers in a very early stage of the implementation process. This allowed us to remove the practical barriers, i.e. attaining access to a computer and the internet, and organise training programs for nurses to improve computer skills. Also, it gave the wards the opportunity to adopt the idea of registration of patient care on a computer. By the time they had to work with the digital registration and feedback system they were already used to the idea of using a computer.

Unfortunately it was not possible to prevent double registration of patient data: nurses had to write patient files and also register the patient daily care in the computer. This is only worthwhile when the digital program is of benefit to the nurses. Therefore, nurses were trained and encouraged to use the feedback provided by the digital program to evaluate and adjust daily care.

The final challenge we want to discuss is the design of the cluster randomised trial. Cluster randomised trials are more complex to perform, as they require more participants [48], due to the correlation between individuals in the same ward. In this study we took this into account by including an intra cluster correlation coefficient in the power calculation. As a result we had to include many hospital patients: 1250 in each group. To include and follow up that many patients in such a short time is ambitious, but we are convinced that it is achievable. Also, analyses of cluster randomised trials are complex. For analysing the effect of an intervention, a regression analysis including covariates should be used to account for the influence of the wards. Therefore this study will consider the following covariates: ward (random effect), institution and the baseline results of the ward.

Dissemination of the results of this study is planned for 2009.

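### With 10 nursing-home wards, the ward effect in the primary Poisson model cannot reliably absorb patient-level overdispersion, so a large-sample test can exceed 5%; a negative binomial model is a cheap improvement

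*Protocol article*

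**What the plan says.** The Statistics section describes the primary comparison in follow-up as a "random effects Poisson regression analysis, including the following covariates: ward (random effect), institution and the baseline results of the ward". The Discussion gives the same list: "this study will consider the following covariates: ward (random effect), institution and the baseline results of the ward". Neither place names a patient-level or dispersion term. Neither says whether institution is fixed or random, or which reference distribution the test uses.

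The primary outcome is the "sum of the incidence of pressure ulcers, urinary tract infections and falls" (Outcome measures). Under that heading:
- Falls are read from patient files, and no limit of one per patient is stated.
- A urinary tract infection takes the patient out of infection registration for a limited time, so a later infection can apparently count again.
- For pressure ulcers, "Patients with an already present PU grade two or worse were only registered if they developed additional PU lesions".

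Study design and setting gives 10 nursing-home wards from six homes and 10 hospital wards from four hospitals. Five wards of each kind received the programme.

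**The concern.** Given the ward, a Poisson model sets the variance of a patient's event count equal to its mean. If some patients fall repeatedly and others never fall, the true variance is larger. Treatment is constant within a ward, so this extra variation reaches the arm comparison through the ward totals. A ward random effect can pick it up there, but only if its variance can be estimated.

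The plan's own covariates leave little information for that estimate. If the ward variance comes out at zero, the standard error falls back to the pure Poisson value. The primary confidence interval and p-value are then too optimistic. This matters most in nursing homes, where falls are expected to dominate the outcome.

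**Working it through.** **Inputs from the article.** The test level is set by "two-sided alpha of 0.05 and 80% power for the analysis of both the hospital and the nursing homes data". The cluster is defined by "As randomisation was on ward level, a ward was considered to be a cluster", and "an intra class correlation coefficient of 0.01 was used in the calculation". Nursing homes: 10 wards, six homes, 100 patients per group (about 20 per ward), 60% expected incidence, target 36%.

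**Assumed, because the article gives no figure.** Patient frailty variance φ from 0 to 4; 0.6 events per patient under the null; homes contributing 2, 2, 2, 2, 1 and 1 wards; equal ward sizes and follow-up; Wald z at 1.96.

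**The plan's own figures.** The article states no type I error to reproduce, but its sample sizes show how the outcome was treated. Hospitals, 12% to 6% as proportions: 356 per group × (1 + 249 × 0.01) = 356 × 3.49 = 1242, which matches the stated 1250. Nursing homes, 60% to 36%: 67 × (1 + 19 × 0.01) = 67 × 1.19 = 80, against the stated 100. A Poisson-rate formula gives 131 × 1.19 = 156. The hospital figure therefore follows from treating each patient as having or not having an event.

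**Residual degrees of freedom for the ward variance.**
- Nursing homes: 10 − (6 institution levels including the intercept + arm + baseline) = 10 − 8 = 2.
- Nursing homes without institution: 10 − 3 = 7.
- Hospitals: 10 − (4 + 1 + 1) = 4.

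**Why the ward variance collapses.** With equal expected counts, the maximum-likelihood ward variance leaves zero only if the ward-level Pearson statistic exceeds the number of wards, 10. That statistic behaves roughly as V × chi-square on the residual df, where V = 1 + 0.6φ is the variance/mean ratio per patient. On 2 df the chance of exceeding 10 is exp(−5/V):
- φ = 0.5: V = 1.3, 2%
- φ = 1: V = 1.6, 4%
- φ = 2: V = 2.2, 10%

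The estimate is thus zero in about 98%, 96% and 90% of trials. Simulation gave about zero in 89–98% over the same range.

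**Simulated nursing-home false-positive rate, Wald z, no true effect** (2000 runs per row, Monte Carlo SE about 0.5 to 1 point; P = Poisson, NB = negative binomial):

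| φ | V | P, no ward effect | P, ward + baseline | P, ward + baseline + institution fixed | NB, ward + baseline | NB, ward + baseline + institution fixed |
|---|---|---|---|---|---|---|
| 0 | 1.0 | 6.7% | 5.2% | 6.5% | 5.0% | 5.9% |
| 0.5 | 1.3 | 11.3% | 8.0% | 11.2% | 5.9% | 7.6% |
| 1 | 1.6 | 15.8% | 10.4% | 14.6% | 6.4% | 8.1% |
| 2 | 2.2 | 22.2% | 13.2% | 21.2% | 6.8% | 8.3% |
| 4 | 3.4 | 33.7% | 15.4% | 29.0% | 7.0% | 8.6% |

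The first Poisson column agrees with theory: 2Φ(−1.96/√(1.19V)) gives 11.5%, 15.5%, 22.6% and 33.0% for φ = 0.5, 1, 2 and 4. With institution fixed, the ward effect recovers little of this up to φ = 2.

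Two further simulations of the institution-fixed model agree broadly. One gave 8%, 12% and 21% at φ = 0.5, 1 and 2, and 8–10% without institution. The other gave 5%, 12%, 16% and 24% at V = 1, 1.5, 2 and 3, against 5%, 6%, 7% and 8% for the negative binomial.

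**Sensitivity.**
- More wards: at φ = 2 with only a ward effect and no patient term, the rate is 11.4% with 10 wards, 5.5% with 40 and 5.6% with 100.
- Poisson with a t reference: 1.9–8.6% on 7 df (no institution) and 0–1.5% on 2 df (institution fixed).
- Negative binomial with a t reference: 1.7–3.0% on 7 df and 0% on 2 df.
- Each patient counted at most once: variance 0.6 × 0.4 = 0.24 against the Poisson 0.60, so the test is conservative.
- Hospitals at V = 1.3–1.6 (250 patients per ward, 0.12 events each): 20–21% for Poisson against 15% for the negative binomial.

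**The case against.** A reader might infer that, without a patient term, repeat events simply count as independent and the error rate must exceed 5%. The article does not support that. The ward effect is the right place for this variation to be absorbed, and with 40 or more wards it is. The excess needs marked patient heterogeneity, few wards and a large-sample test all together.

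Repeat counting is also not certain. The power calculation uses percentages. The pressure-ulcer sentence says when a patient with an existing ulcer is registered, not that each new lesion is counted. If patients count once, the error goes the other way.

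The reference distribution is unstated, and a condensed article may leave it to the full plan. A t reference on 2 df removes the excess with no patient term.

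These points stand, and they make the size conditional. They do not remove the point, for two reasons. First, the model's terms are stated twice, so the criticism concerns what is written. Second, t on 2 df is a costly rescue. At the planned effect (60 against 36 events), the Poisson standard error of the log rate ratio is √(1/60 + 1/36) = 0.211, so z = 0.511/0.211 = 2.42 against a critical value of 4.30. That is roughly 3% power even before overdispersion. Without institution, t on 7 df still reaches 8.6% at φ = 4.

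**Conclusion.** The point holds in conditional form. For φ between 0.5 and 4, the stated model with a Wald z test can give a nursing-home false-positive rate of about 8–15% with ward and baseline. With institution as a fixed effect it gives about 8–29%, where the low end spans the simulations at φ = 0.5. With truly Poisson counts there is essentially no inflation (5.2% and 6.5%).

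These figures rest on an assumed dispersion, an assumed z reference, institution read as fixed because only ward is labelled random, an assumed ward layout, and repeat events being counted. In hospitals, most of the excess remains after the model is changed (15% of 20–21%), so there it is chiefly a few-wards problem. Confidence is medium. This is a worthwhile, inexpensive improvement, not proof that the primary analysis is invalid.

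**What to change.** Fit the primary model at patient level as a negative binomial regression, or as Poisson with a patient-level random intercept. Keep the ward random effect, institution and ward baseline result, and report the estimated dispersion. State also whether a patient's repeat events are all counted.

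Pair the model with a named small-sample method for ward-level inference, because with a z test it still leaves about 6–9% once institution is fixed and φ is at least 0.5. Choose that method with care: a plain t on the residual df overcorrects (1.7–3.0% on 7 df, 0% on 2 df). A short simulation on the actual ward layout before the analysis would settle the choice.

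The change takes a sentence or two in the analysis plan and no new data. Its price is wider intervals when repeat events are common.

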## Discussion

As implementation of a guideline is time-consuming, it is difficult for organisations to implement all available guidelines. Also, lack of feedback about performance using quality indicators of guideline based care and lack of a recognisable, unambiguous system for implementation often impede guideline implementation. A program that allows organisations to implement multiple guidelines simultaneously may facilitate guideline use and thus improve patient safety.

This study posed several challenges concerning the development of the complex intervention, the implementation of this intervention and the design of the trial. For the development of our intervention we used available guidelines on each topic. Translating three extensive guidelines into a manageable proposal for improving patient care is not easy. We chose to combine the essence of each guideline into a recognizable simple structural approach, and reduced the guidelines on each topic into two or three bundles. These bundles were easier to use in daily practice. The aim of the digital registration and feedback system was to provide the nurses on the ward with feedback on the performance of guideline based care. As we anticipated that nurses have limited computer skills and limited time to register all patients daily, we paid extra attention to the accessibility and performance of the digital program. This program was subsequently pre-tested during the first phase of this study in a group of future users and it was obvious that we had managed to develop a digital registration and feedback system that was user-friendly for all nurses on the wards. Also, the time it takes to register all patients on the wards was considered acceptable.

Our next challenge was the implementation of our intervention. Many factors may enhance or inhibit implementation. Therefore it is important to analyse the target group [16]. To be successful, we developed a multifaceted implementation strategy that could be tailored to each specific ward. By tailoring the strategy to the barriers of the individual wards we developed an individual implementation plan for each ward that considered the context of that particular ward.

The implementation of the digital registration and feedback system was even more complex. Currently, registration of patient care in a computer is not a standard procedure in the Netherlands. The nursing files are still mainly paper files. Moreover, not all nurses of the participating wards were used to working with a computer and on some wards the nurses did not even have access to a computer or the internet. We explored these barriers in a very early stage of the implementation process. This allowed us to remove the practical barriers, i.e. attaining access to a computer and the internet, and organise training programs for nurses to improve computer skills. Also, it gave the wards the opportunity to adopt the idea of registration of patient care on a computer. By the time they had to work with the digital registration and feedback system they were already used to the idea of using a computer.

Unfortunately it was not possible to prevent double registration of patient data: nurses had to write patient files and also register the patient daily care in the computer. This is only worthwhile when the digital program is of benefit to the nurses. Therefore, nurses were trained and encouraged to use the feedback provided by the digital program to evaluate and adjust daily care.

The final challenge we want to discuss is the design of the cluster randomised trial. Cluster randomised trials are more complex to perform, as they require more participants [48], due to the correlation between individuals in the same ward. In this study we took this into account by including an intra cluster correlation coefficient in the power calculation. As a result we had to include many hospital patients: 1250 in each group. To include and follow up that many patients in such a short time is ambitious, but we are convinced that it is achievable. Also, analyses of cluster randomised trials are complex. For analysing the effect of an intervention, a regression analysis including covariates should be used to account for the influence of the wards. Therefore this study will consider the following covariates: ward (random effect), institution and the baseline results of the ward.

Dissemination of the results of this study is planned for 2009.
